This pilot study of MME collaborates with health clinics offering antenatal services under the Greater Gaborone District Health Management Team (GGDHMT) to conduct a pragmatic clinical trial [68, 69] of an innovative, culturally tailored stigma reduction intervention among pregnant mothers diagnosed with HIV. The intervention builds on prior evidence-based strategies while also integrating WMM for pregnant mothers in Botswana (see “Intervention rationale and components”). We named our intervention “MME” (pronounced “mm-eh”), short for “Mothers Moving towards Empowerment.” *Mme* is also a Setswana term used to address a respected woman. We utilize a pragmatic study design that retains all core elements except for randomization, which was not feasible among this complex population where we must group together women who are at approximately the same stage of pregnancy at the same time. Instead, we use systematic assignment by the experimenter to MME or a control group receiving treatment as usual (TAU). We measure primary and secondary outcomes at three time points (pre-intervention, immediately post-intervention, and at 16-week follow-up postpartum). All details regarding the protocol sections can be located through the SPIRIT checklist (Additional file 1).

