### Assessments and outcome measures

All assessments are enumerated in Table 1, including their domain (name of the outcome), specific measurement, metric, method of aggregation, and time points. The three main time points are (1) baseline (< 28 weeks gestational age), post-intervention (immediately following completion of 8-session intervention, intervention group only), and follow-up (16 weeks postpartum). Primary outcomes for the mother include HIV stigma, psychosocial outcomes, treatment adherence, and HIV outcomes (e.g., viral load). Secondary outcomes for the infant include birth outcomes and early infant health. Stigma and psychosocial outcomes are collected via self-report questionnaires; all other outcomes are collected via health/medical records for the mother and infant. In addition, there are no additional studies using participants’ data and there are also no biological specimens that will be collected. If there are other studies to be conducted, there will be a separate procedure for additional consent.

**Table 1 Tab1:** Overview of measures

Assessment measure	Baseline (< 28 weeks gestational age)	Post-MME	Follow-up (16 weeks postpartum)	Comparison metric

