**Covariates**				
Demographic measures	ALL	MME	ALL	N/A
Alcohol use (AUDIT)	ALL	MME	ALL	N/A
Sexual behavior (5 items)	ALL	MME	ALL	N/A
Intimate partner violence (WAST)	ALL	MME	ALL	N/A
**Qualitative** (open-ended; differs at each time points)	MME	MME	MME	N/A
**HIV metrics:** CD4 count and viral load (IDCC records/electronic medical record system)			ALL	1
**Birth outcomes:** birth weight, gestational age, APGAR scores (Delivery Summary Sheet)			ALL	1
**Infant health:** infant mortality, infant HIV status, feeding method, vaccinations, hospitalizations (dates, diagnosis) (“Under 5 Card”: asked from mother at 4 month follow-up)			ALL	1

1 Bivariate comparison of mean (median) scores at 16-week follow-up between intervention and control group

2 Bivariate comparison of change in mean (median) scores from baseline to 16-week follow-up between intervention and control groups

3 Bivariate comparison of mean (median) scores at baseline and post-MME within intervention group

4 Bivariate comparison of mean (median) scores at baseline and 16-week follow-up within intervention group

5 Bivariate comparison of mean (median) scores at post-MME and 16-week follow-up within intervention group

*ALL* all participants

*MME* only intervention participants

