We will then build exploratory linear (continuous outcomes) or logistic (dichotomous outcomes) regression models to examine the effect of study arm on primary and secondary outcomes, and examine mediating effects of stigma on primary outcomes in mothers and exploratory outcomes in infants. We will prioritize objective measures in examining antenatal and ART outcomes and use self-report measures as a check on these findings. We will examine changes in predictors (e.g., stigma) between time points by creating difference variables and also examine these predictors as time-varying covariates in the regression model using generalized estimating equations (GEE) and structural equation models (SEM). A focus will be to examine whether changes in primary outcomes in mothers from baseline to post-intervention predict changes in primary outcomes at follow-up. If possible, SEM will also be used to examine structural relationships between latent constructs in the conceptual framework (e.g., among stigma subscales) and measured variables. Statistical significance will be assessed as *p* < 0.05. Statistical analysis will be conducted in Stata 16.

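### Testing early change against follow-up change in the same outcome has no valid zero null, because with three visits the two differences share a score

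*Protocol article*

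**What the plan says.** The Introduction of the protocol article fixes the measurement occasions: "We measure primary and secondary outcomes at three time points (pre-intervention, immediately post-intervention, and at 16-week follow-up postpartum". The section Assessments and outcome measures restricts the middle one to the MME arm: "post-intervention (immediately following completion of 8-session intervention, intervention group only".

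The Statistical analysis section codes change as raw differences, "We will examine changes in predictors (e.g., stigma) between time points by creating difference variables", and also mentions time-varying covariates in GEE and SEM. It then states the question at issue, "A focus will be to examine whether changes in primary outcomes in mothers from baseline to post-intervention predict changes in primary outcomes at follow-up", and the criterion, "Statistical significance will be assessed as *p* < 0.05". These regression models are introduced as exploratory.

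The section does not say where a change at follow-up starts. The notes to Table 1 use both possible starts within the MME arm: "Bivariate comparison of mean (median) scores at baseline and 16-week follow-up within intervention group" (metric 4) and "5 Bivariate comparison of mean (median) scores at post-MME and 16-week follow-up within intervention group" (metric 5). Nor does it say whether the predictor and the response are the same outcome or different ones.

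**The concern.** With three scores per woman (baseline, post-MME, follow-up), early change is post-MME minus baseline. Follow-up change in the same outcome can only be follow-up minus post-MME, which reuses the post-MME score with the opposite sign, or follow-up minus baseline, which reuses the baseline score with the same sign. Noise in the shared score enters both variables. Zero is then not the value expected when early change carries no information about later change, so a test against zero does not answer the stated question.

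At stake is how durability is read. With baseline as the start, early improvers tend to look better at follow-up. With post-MME as the start, the same women tend to look as if they relapse. Either pattern can arise from visit noise alone, and the Discussion says the results will inform refinement of MME and a larger randomised trial.

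**Working it through.** **Inputs from the protocol article.** Three visits; difference variables; alpha 0.05 (Statistical analysis), two-sided (Sample size and power). The same section gives an example of 15 MME women, an example total of 40 for a correlation, and a 3:1 ratio. No total sample size is stated, so 40 × 3/4 = 30 MME women is an assumption.

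**Assumptions not in the documents.** Normal scores, equal variance across visits, and the noise structures named below.

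**1. The plan's own correlation figure.** For n = 40 and correlation 0.45, Fisher z gives atanh(0.45) × √37 = 0.485 × 6.083 = 2.948. Subtracting 1.960 leaves 0.988, or 84% power. Allowing for the larger variance of the Spearman coefficient gives 82%, and simulation of the Spearman test (40,000 samples) gives 80.1%. The stated power of over 80% is reproduced.

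**2. Same outcome, no real link.** Let Y_t = T + e_t, with T stable and the e_t independent with variance v.
- Predictor: Y1 - Y0 = e1 - e0, variance 2v.
- Follow-up minus post-MME: cov(e1 - e0, e2 - e1) = -v, so the correlation is -v/2v = -0.5.
- Follow-up minus baseline: cov(e1 - e0, e2 - e0) = +v, so the correlation is +0.5.

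T cancels, so under this model the result does not depend on reliability. The artefact of 0.5 is larger than the 0.45 that the plan treats as detectable.

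**3. Rejection rate at nominal 5%** (20,000 simulated samples; nearly the same for both start points):

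| MME women | Regression/Pearson | Spearman |
|---|---|---|
| 15 | 50% | 44% |
| 20 | 64% | 57% |
| 30 | 83% | 77% |
| 40 | 92% | 89% |

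Hand check by Fisher z, with atanh(0.5) = 0.549: at n = 15, 0.549 × √12 - 1.960 = -0.06, about 48%; at n = 30, 0.549 × √27 - 1.960 = 0.89, about 81%.

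**4. Other error structures.**
- Persistent woman-specific change, unrelated to later change, with variance 2v: the predictor has variance 4v, so the correlation with follow-up minus post-MME is -v/√(4v × 2v) = -0.35. Rejection is about 26% at 15 women and 50% at 30.
- AR(1) scores with lag-1 correlation ρ: the correlations are -(1 - ρ)/2 for follow-up minus post-MME and √(1 + ρ)/2 for follow-up minus baseline. Simulated at 30 women:

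| ρ | Follow-up minus post-MME | Follow-up minus baseline |
|---|---|---|
| 0.5 | r = -0.25, 27% | r = 0.60, 97% |
| 0.8 | r = -0.10, 8% | r = 0.67, 99% |
| 0.95 | about -0.02, 5% | r = 0.69, over 99% |

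Follow-up minus baseline equals early change plus later change. It contains the predictor, so zero is a poor reference for it throughout.

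**5. Different outcomes.** If the second outcome has noise u_t that correlates with e_t at r within a visit, the covariance comes only from the shared visit and the correlation is -r/2 or +r/2. Rejection rates:

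| r (assumed) | 15 women | 30 women |
|---|---|---|
| 0 | 5% | 5% |
| 0.3 | 8% | 12% |
| 0.5 | 14% | 27% |
| 0.7 | about 25% | 49% |

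**6. Would adding baseline as a covariate repair the same-outcome test?** Not in general. At 30 women, follow-up minus post-MME still rejected 86-99%. Follow-up minus baseline held 5% only with no stable between-woman variance, and rejected 42-70% when that share was 0.5-0.8.

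**The case against.** The strongest reply is that the sentence does not say predictor and response are the same outcome. The same section speaks of stigma as a predictor and a mediator, and the Abstract hypothesises that self-stigma mediates psychological outcomes and adherence. A change in stigma and a change in depression share no score. A reader might infer that every change-on-change test here is false by construction and that noise alone will produce a significant predictor. The documents do not support that: for different outcomes with independent noise the rate is 5%, and the inflated rates rest on noise correlations that appear nowhere in the protocol. Correlated noise is plausible between self-report scales completed at one visit, and less so between a stigma scale and antenatal visits read from the clinic card.

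Second, the 0.5 figure needs stable scores with independent noise, in a trial meant to produce change. This also stands: step 4 shows the artefact shrinking, and under strong autocorrelation nearly vanishing, for follow-up minus post-MME. It does not vanish for follow-up minus baseline.

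Third, the article condenses a fuller plan, labels the models exploratory and names GEE and SEM. The exact model may well be set elsewhere, and its absence is not the point. But any same-outcome analysis built on the stated difference variables and three visits must overlap, whichever start is chosen. Naming GEE or SEM does not change this unless error is modelled separately, and no such model is stated for this question. The exploratory label limits the consequences but does not correct the null.

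**Conclusion.** The point holds for same-outcome pairs. Under stable scores with independent, equal-variance visit noise and no real link, the planned comparison has an expected correlation of about -0.5 or +0.5 and rejects about 50% of the time at 15 MME women and about 83% at an assumed 30. The sign follows from an unstated choice of start point, and the size depends on the error structure.

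For different outcomes the problem is conditional: none if same-visit noise is independent, and about 12-49% rejection at 30 women if it correlates at an assumed 0.3-0.7. These are probabilities under stated models; they do not mean that a significant result is certain. The between-arm comparison is unaffected. The change is worth making because this is the question the plan singles out for linking early response to postpartum results.

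**What to change.** Re-specify the focus analysis in the Statistical analysis section:

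1. **Same outcome.** Do not test raw change against raw change versus zero, and do not read such an association as prediction. Describe the trajectory over the three visits in MME women.
2. **Different outcomes.** Name the pairs. In MME women, regress the 16-week level of the outcome on the post-MME level of the predictor, adjusting for the baseline predictor and for the baseline and post-MME outcome. Report the coefficient with a 95% confidence interval as exploratory.

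This uses data already scheduled and costs only wording and a different model. The downside is three extra covariates: with an intercept and four predictors, 15 women leave 10 residual degrees of freedom and 30 leave 25, so intervals will be wide. The claim that early change predicts later change in the same outcome is given up.

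The level model is also only approximately valid, because its covariates are noisy. In most simulated no-link settings at these sizes it rejected 4-6%, rising to 7-8% at 30 women when the stable parts of the two outcomes correlated at 0.7 and their noise did not. At 200 women the rate was about 12% in one unfavourable setting and 42% in another, so the residual bias should be acknowledged, above all if the model is carried into a larger trial.

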### Sample size and power

Power calculations were done using Power Analysis and Sample Size Software (PASS 2019) [99]. Given the exploratory and pragmatic nature of the study, we calculated power based on the Wilcoxon rank-sum (Mann-Whitney *U*) test for primary outcomes (measured continuously) based on an intent-to-treat analysis. We assume a 3:1 rate of intervention to control participants. Example group sample sizes of 5 (control) and 15 (intervention) achieve > 85% power to detect a median difference of 1.0 using a two-sided Mann-Whitney *U* or Wilcoxon rank-sum test assuming that the actual data distribution is normal when the significance level (alpha) of the test is 0.05 [100–104]. An example sample size of 40 achieves > 80% power to detect a Spearman rank correlation of >|0.45| using a two-sided hypothesis test with a significance level of 0.05. These results are based on 5000 Monte Carlo samples from the bivariate normal distribution under the alternative hypothesis [105, 106]. We will also calculate power post hoc based on the data collected in this study (actual sample size and effect size) before we begin analysis.

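### The >85% power for 5 v 15 women rests on a difference of 1.0 with no SD or scale: it needs about 1.75 to 1.8 SD, and is about 39% if 1.0 means one SD

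*Protocol article*

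**What the plan says.** All of this is in the protocol article, section *Sample size and power*. The calculation covers the continuous primary outcomes as a class, analysed by intention to treat with the rank-sum test. The allocation is fixed first: "We assume a 3:1 rate of intervention to control participants". Then comes the only between-arm power figure in the document: "Example group sample sizes of 5 (control) and 15 (intervention) achieve" more than "85% power to detect a median difference of 1.0 using a two-sided Mann-Whitney" or Wilcoxon rank-sum test, "assuming that the actual data distribution is normal" and "when the significance level (alpha) of the test is 0.05".

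The section names no outcome for the 1.0, gives no SD, and does not say that the difference is standardised. It adds a second example, a Spearman correlation with a sample of 40. It closes with a promise to "calculate power post hoc based on the data collected in this study (actual sample size and effect size) before we begin analysis".

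The continuous primary outcomes are described under *Stigma* and *Psychosocial outcomes*: stigma scales of 40 and 20 items plus three Botho items, and psychosocial measures of 20, 12, 8, 8 and 6 items.

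**The concern.** Under a normal shift, the power of a rank-sum test depends on the difference divided by the SD. A difference of 1.0 without an SD therefore fixes no power. One value is applied to scales of very different length, which makes a standardised unit the natural reading. On that reading, 20 women split 5 to 15 look far too few for 85%.

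The pilot is meant to inform refinement of the intervention and a later multisite randomised trial. A reader who takes the figure at face value would credit the between-arm comparison with much more sensitivity than it has for a one-SD effect.

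The post hoc sentence raises a separate problem. The actual effect size is the between-arm result, so it cannot be known before the analysis starts.

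**Working it through.** **Inputs from *Sample size and power*.** n1 = 5 control, n2 = 15 intervention, two-sided alpha 0.05, normal data, difference 1.0, rank-sum test. The SD is not stated. It is treated here as an assumption and varied from 0.5 to 2.0. Write d = 1.0/SD.

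**The plan's own figure.** More than 85% can be neither reproduced nor refuted from the stated inputs, because d is undetermined. The useful question is which d would produce it.

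**Simple bound.** For the z formula, power ≈ Φ(d·√(n1·n2/(n1+n2)) − 1.960).
- √(5 × 15/20) = √3.75 = 1.936.
- At d = 1: Φ(1.936 − 1.960) = Φ(−0.024) = 49.1%.
- For 85% power: d = (1.960 + 1.036)/1.936 = 1.55.

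This formula is generous at such small n, yet it already needs about one and a half SDs.

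**Rank-sum test.** Power by simulation, 100,000 normal samples per row:

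| Assumed SD | d | Exact test | Normal approximation, uncorrected |
|---|---|---|---|
| 2.0 | 0.5 | 12.8% | 15.2% |
| 1.0 | 1.0 | 38.7% | 42.9% |
| 0.667 | 1.5 | 72.2% | 75.9% |
| 0.588 | 1.7 | 82.3% | 85.3% |
| 0.571 | 1.75 | 84.5% | 87.0% |
| 0.556 | 1.8 | 86.6% | 88.9% |
| 0.5 | 2.0 | 92.4% | 94.0% |

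The exact test passes 85% between d = 1.75 and d = 1.8. The uncorrected approximation passes it at about d = 1.7. At d = 1 no other variant comes close: the t-test gives 45.0% and even a one-sided rank-sum test gives 55.8%.

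**Numbers needed at 1.0 SD with 3:1 allocation (exact test).** 10 v 30 gives about 73 to 74%, 12 v 36 about 81%, 13 v 39 about 84%, and 14 v 42 about 87%. At 10 v 30, the difference detectable with 80% power is about 1.1 SD.

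**Spearman statement.** At n = 40 and rho = 0.45, simulation gives 79.6 to 80.1%. The stated figure reproduces within simulation error.

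**Post hoc power.** For a z-type test, observed power = Φ(|z| − 1.960) + Φ(−|z| − 1.960). At p = 0.05, |z| = 1.960, so observed power = Φ(0) + Φ(−3.92) ≈ 50%, whatever the sample size. It is a function of the p-value alone and needs the observed arm contrast as its input.

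**The case against.** A reader might infer that the >85% is simply an arithmetic error. The document does not support that. It never says that 1.0 is in SD units, and an SD of about 0.57 or less makes the figure correct. Nor does the differing number of items force the standardised reading. If the scales were scored as item means, length would drop out, and a raw difference of 1.0 with an SD near 0.5 to 0.6 would be coherent. The text does not say whether scores are sums or means. This part of the objection stands, and the conclusion has to be conditional.

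It could also be said that a journal article condenses a fuller protocol, which may hold the SD. That is possible. But the article chose to publish a power figure with its effect size, and without the SD or the unit that figure tells its readers nothing definite. Asking for the missing quantity is fair.

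Two further inferences should be resisted. The first is that totals of 20 and 40 in the two statements contradict each other. Both are labelled examples, neither is an enrolment target, and they serve different tests. The second is that a null result would necessarily count against the intervention. The protocol calls this a pilot and nowhere says so.

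Finally, the post hoc sentence changes no test or estimate. That is true, and it limits the severity, but the sentence still prescribes something that cannot be done in the stated order.

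**Conclusion.** The point holds in conditional form. As written, the power figure is unverifiable. It is met only for a standardised difference of about 1.75 to 1.8 or more with the exact test (about 1.7 with an uncorrected normal approximation), equivalent to an SD of about 0.57 or less. If 1.0 means one SD, which best fits one value covering every continuous primary scale, power is about 39%. A reader of the section cannot tell which case applies, although either answer changes how the comparison should be read.

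These figures assume independent normal observations with equal SDs and complete data for all 20 women. Missing outcomes, or correlation within intervention groups, would lower them.

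The post hoc power plan is faulty whatever the SD: it contradicts itself on timing and adds nothing to the p-value. The example sample sizes and the Spearman statement are not errors. Severity is moderate.

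**What to change.** 1. Restate the between-arm figure as a standardised effect, for example: *with 5 control and 15 intervention women, more than 85% power requires a difference of about 1.8 SD; power for 1.0 SD is about 39%*. Alternatively, keep 1.0 and state the outcome, its scoring and the SD that justify it.
2. If a total of 40 is expected, add the detectable effect at 10 v 30: about 1.1 SD with 80% power.
3. Delete the sentence on post hoc power. Report between-arm differences, for example Hodges-Lehmann estimates, with 95% confidence intervals, which show directly which effects the data leave open.

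The cost is wording only. No extra women are needed and no planned test changes. If the standardised form is used, the stated power becomes less favourable.

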## Discussion

We take advantage of this rare opportunity to adapt, train, and evaluate a culturally based, HIV stigma reduction intervention to maintain ART adherence among those who are especially vulnerable—pregnant women with HIV. In the context of Botswana, a country with high HIV prevalence but also national programs to provide free ART and antenatal care [107], reducing stigma addresses a core barrier to postpartum ART adherence for women living with HIV. While increasing efforts have been made to learn how to reduce stigma and increase adherence for this vulnerable population, very few interventions have been shown to reduce HIV stigma into the postpartum period. Due to structural conditions, women face greater vulnerability to stigma because routine testing for HIV during antenatal care leads women to more frequently be identified as having HIV before their male partners and consequently be blamed for bringing HIV to the relationship. Based on our formative qualitative work to adapt the MME intervention for what matters most for women, we find that the desire to fulfill “being a good mother” may motivate mothers to remain ART-adherent when pregnant [24] but could wane postpartum and is threatened by these sources of stigma. We aim to extend positive effects of our culturally tailored stigma intervention into postpartum by both countering harmful stereotypes and informing about the benefits of continued ART postpartum. By doing so, we aim to reduce stigma, improve psychosocial outcomes, and maintain treatment adherence among women who have been identified as having HIV during pregnancy. We will also consider the potential intergenerational benefits for infants, not only in reducing mother-to-child transmission of HIV but for other birth and early health outcomes [108].

Potential limitations of this study start with challenges in recruitment and retention. From the outset, difficulties in recruiting only primiparous women led us to expand our criteria to multiparous women. However, we can imagine women who have previously given birth may differ from those who have not. The challenges of rolling recruitment of pregnant women during the narrow window of eligibility of the first 28 weeks have also prevented us from randomizing the treatment and control groups; however, we are still allocating participants to groups systematically and will adjust for any baseline differences in analyses. Pregnant women have many competing demands on their time and so it can be challenging to participate in an 8-session program. We have been responsive to requests from groups that are interested in having sessions twice weekly. It would also be helpful to know which aspects of the interventions were most effective; however, since the components are integrated together, we will not be able to isolate the effects to specific components. Given the formative work and adaptation to this specific context, whether the findings themselves are generalizable must be empirically tested; however, the approach and standardized methods we have developed can be used to replicate the process in new settings. Finally, the child outcomes are exploratory, but if promising, then future studies should be powered to detect clinically meaningful differences in these variables.

Currently, little is known about how to reduce HIV stigma that interferes with postpartum treatment in a context of free antenatal care and ART treatment. This study offers a model for how to use formative research and the WMM theoretical framework to identify culturally meaningful aspects of stigma and adapt evidence-based stigma reduction intervention components for women living with HIV in Botswana. While we realize that changing stigma in other stakeholders (e.g., family, community members, healthcare providers) is crucial, here we choose to alleviate stigma among pregnant women living with HIV whom we have identified as having particular vulnerabilities towards stigma, in part due to inadvertent effects of current HIV treatment policies. The intervention explicitly focuses on this by helping women resist stigma that threatens their moral standing in the community and emphasizes how continued ART during postpartum contributes to being a good mother. By training peer co-leaders, we build on existing resources and enhance local capacity. We envision a cohort of local trainers with the ability to sustain the work and continue to reach women after the study ends. Finally, we are conducting a rigorous evaluation of the intervention. To our knowledge, this is one of the first studies to systematically evaluate a stigma reduction intervention using a peer contact-based approach in sub-Saharan Africa [35], and has the potential to be one of the only stigma interventions to show stigma-reducing effects into the postpartum period. We use the most robust pragmatic study design that is feasible in terms of recruitment and implementation. Although we lack randomization, we include a control group, systematically allocate to intervention or control, blind all research staff except those administering the intervention, conduct assessments at multiple time points, include both subjective and objective measures of health and wellbeing, and consider potential intergenerational effects with both mother and infant outcomes. We also track process outcomes including fidelity and dosage. Together, this will help inform further refinement of the MME intervention and preparation for a large-scale, multisite, randomized controlled trial in the future.

